### 4.5.1. Selection of participants

There will be no exceptions to eligibility requirements at the time of randomisation. Questions about eligibility criteria must be addressed to the trial management group prior to attempting to randomise the participant.

The eligibility criteria are the standards used to ensure that only medically appropriate mothers and neonates are considered for this trial. Mothers or neonates not meeting the criteria should not join the trial. For the safety of the participants, as well as to ensure that the results of this trial can be useful for making treatment decisions regarding other mothers/neonates in similar situations, it is important that no exceptions be made to these criteria for admission to the trial.

Those enrolled in the trial will be those who have been admitted to hospital. Mothers or neonates will be considered eligible for enrolment in this trial if they fulfil all the inclusion criteria and none of the exclusion criteria as defined below.

#### 4.5.1.1. Patient inclusion criteria

*Mothers:*

1. Presenting in labour with or without rupture of membranes

*Neonates:*

1. Born in a healthcare facility
2. Postnatal age at randomisation <24 hours
3. Birth weight >1000g

**4.5.1.2. Patient exclusion criteria***Mothers:*

1. Under the age of 18 (minor in Malawi)
2. Any contra-indication to digital vaginal examination
3. In active labour (regular contractions and/or cervical dilatation of more than 4cm)
4. Poor perineal and vaginal skin condition as judged by clinician
5. Planned elective caesarean-section delivery
6. Known or suspected allergy to chlorhexidine or octenidine or phenoxyethanol
7. Intrauterine death confirmed or expected before randomisation
8. Antiseptic application or enrolment in the trial determined inappropriate in the opinion of the enrolling clinician
9. Any recent or planned (within 4 hours) iodine application to the perineum or vagina
10. Unable to obtain consent

*Neonates:*

1. Born by planned elective caesarean section
2. Born to mothers recruited in the trial
3. Poor skin condition (skin score of 2 or more in any of three domains (see [Appendix I](#))) at the time of enrolment
4. Known congenital or acquired skin disorder or defect at time of enrolment
5. Antiseptic application or enrolment in the trial determined inappropriate in the opinion of the enrolling clinician
6. Any recent or planned (within 4 hours) iodine application to body
7. Any planned or previous lumbar puncture
8. Unable to obtain parental or guardian consent

**4.5.2. Co-enrolment guidelines**

Co-enrolment in previous or future trials is considered in [Section 4.5.5.3](#).

**4.5.3. Informed consent and withdrawal of consent**

Posters advertising the trial will be displayed in the antenatal ward, antenatal clinic and labour ward of Zomba Central Hospital. Where possible, information about the trial will be given antenatally. The poster contains the contact information of the coinvestigator and consultant obstetrician at Zomba Central Hospital for the trial team, for pregnant women or parents/carers who wish to obtain more information.

*Maternal - Participant approach and consent:*

Before the research midwife approaches a woman about the trial, she will check with the clinical team if there is any reason that this would be inappropriate. The clinical team will therefore act as gatekeepers for any participants, ensuring that they are both eligible and considered to be in a stable mental and physical condition before being approached, preventing unwanted disturbance.

Women who are already known to be in active labour will not be approached by the research midwife, and will not be eligible for inclusion.

Women who have been deemed appropriate for being approached will then be provided with a participant information leaflet, in a language they understand. The trial and the contents of the participant information leaflet will be verbally explained to them and they will be free to ask any questions. The women may take as much time as they need to discuss with their partners and consider joining the trial; but will be made aware that women in active labour will not be eligible for inclusion.

*Newborns:*

Parents/carers of newborns will be given information about the trial including a participant information leaflet in a language they understand. They will have the trial and contents of the participant information leaflet verbally explained to them and will be free to ask any questions about the trial. They may take as much time as they need to consider joining the trial, but will be made aware that only babies up to 24 hours old can be enrolled.

*Both:*

The doctor or midwife seeking consent, who will be fully trained in consent procedures, will confirm understanding of the important points of the trial.

It will be made completely and unambiguously clear that participation is voluntary and the labouring woman or parent/carer is free to refuse to participate in all or any aspect of the trial, at any time and for any reason, without incurring any penalty or affecting the treatment of the Mother or the baby.

Only following this formal written consent can be sought. Signed consent will be kept by the investigator and documented in both the labouring woman's and the neonate's notes and a copy given to the participant or neonate's parent/carer. Consent may be given using a thumbprint with signed agreement from an independent witness.

If a participant or newborn's parent/carer chooses to discontinue trial treatment but remains willing to follow other trial procedures and follow-up schedule, the participant may remain in the trial "on-study, off-study treatment". However, if they do not wish to remain on trial follow-up, their decision must be respected and the participant will be withdrawn from trial follow-up. The sponsor should be informed of this in writing using the appropriate documentation. Prior to transferring to routine follow-up, the participant or parent/carer will be asked whether they would be happy to have assessments performed as for the final study visit. They would be at liberty to refuse any or all individual components of the follow-up assessments and their wishes should be respected.

If follow-up is stopped early, the pseudonymised medical data collected during their participation in the trial will be kept and used in the analysis of the trial results; consent cannot be withdrawn for the use of historical pseudonymised data already collected.

#### **4.5.4. Pre-randomisation procedures**

Written informed consent to enter into the trial and be randomised will be obtained from Mothers (for their own participation) or parents/carers (for neonate participation) after explanation of the aims, methods, benefits and potential hazards of the trial and before any trial-specific procedures are performed.

For enrolment to the maternal stratum: mothers will be approached on admission to the labour ward, and when initial routine clinical procedures and communication have already been completed. For enrolment to the neonatal stratum: parents/carers will be approached after their baby has been admitted to the neonatal or post natal ward, and after initial routine clinical procedures and communication have been completed.

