#### **4.5.5. Randomisation**

##### **4.5.5.1. Randomisation practicalities**

Randomisation will be performed using a random number generated as implemented in the statistical computing environment R. Randomisation will be by permuted blocks (random block sizes of 7 or 14 participants) to guard against bias introduced over time, such as outbreaks of pathogenic bacteria in the hospital. Participants will be randomised 1:1:1:1:1:1 to the 6 treatment and 1 control arms.

Randomisation will be built into electronic data systems using algorithms developed by the data management team at the Malawi Liverpool Wellcome Trust (MLW). The participant's trial number, treatment allocation and the date of randomisation will be entered into the trial register at the site.

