#### **4.10.4. Analysis plan (brief)**

The analyses will be described in detail in a full Statistical Analysis Plan. This section summarises the main issues.

The primary analysis population is intention-to-treat, including all randomised participants, regardless of treatment received. This corresponds to estimating the impact of the effectiveness of the treatments. However, in secondary analyses we will also use inverse-probability weighting methods to adjust for deviation from randomised strategy, which is a more efficient approach than defining a per-protocol population.

Analysis of the co-primary endpoints will compare within-individual differences over time across randomised arm to maximise the information gained from the trial. Analysis will use linear mixed-models, with individual as a random effect, will adjust for baseline values of each outcome, and use Normally distributed errors. Analysis will be both frequentist, enabling straightforward comparison between arms (primary analysis since sample size is based on this), and Bayesian, enabling estimation of the probability that one arm is truly superior to another. This is more powerful when sample sizes are small as use of priors provides additional information. Sensitivity analysis to prior assumptions will be performed using optimistic, non-informative and sceptical priors.

The effect of each treatment arm will be assessed within a single model with each factor being fitted independently as a factor, and not as a continuous variable. Comparison of main effects within arms will be assessed using the estimate and 95% confidence interval of the comparison of differences between factors and in comparison, to control. As this is a pilot trial, the sample size was not powered to robustly detect interactions between treatment and frequency and so we will not test these formally, but will use exploratory analyses to assess whether there is any evidence supporting individual interactions testing each one, one at a time.

Similar mixed models will be used to analyse change in skin temperature after vs before each application, including individual as a random effect, the change in temperature as the outcome and the pre-application (baseline) temperature as a factor.

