#### Neonatal strata

1. Born by planned elective caesarean section
2. Born to mothers recruited in the trial
3. Poor skin condition (skin score of 2 or more in any of three domains (see [Appendix I](#))) at the time of enrolment
4. Known congenital or acquired skin disorder or defect at time of enrolment
5. Antiseptic application or enrolment in the trial determined inappropriate in the opinion of the enrolling clinician
6. Any recent or planned (within 4 hours) iodine application to body
7. Any planned or previous lumbar puncture
8. Unable to obtain parental or guardian consent

The primary analysis population is intention-to-treat, including all randomised babies, regardless of treatment received. This corresponds to estimating the impact of the effectiveness of the treatments. However, in secondary analyses we will also use inverse-probability weighting methods to adjust for deviation from randomised strategy if non-compliance rates are >15%, which is a more efficient approach than defining a per-protocol population (1).

Loss-to-follow rates are unknown but may be high as participants may give birth (in the maternal strata) or be discharged (in the neonatal strata) before all planned swabs are taken. Missing swabs

will be monitored and participants without baseline and two post-baseline swabs may be replaced to maintain power. However, all baseline and post-baseline results will be included in analyses.

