## Neonatal

- Prolonged rupture of membranes (>18h): n(%) yes, no, unknown
- Offensive liquor: n(%) yes, no, unknown
- Mother received antibiotics in labour: n(%) yes, no, unknown
- Mode of delivery: n(%) vaginal spontaneous, vaginal assisted, emergency caesarean section
- Maternal HIV status: n(%) positive, negative, unknown
- Age at enrolment (hours): median (IQR)
- Estimated gestational age at labour: median (IQR)
- Sex: n(%) male, female
- AGPAR Score at 1 minute: median (IQR)
- AGPAR Score at 5 minutes: median (IQR)
- AGPAR Score at 10 minutes: median (IQR)
- Where admitted: n(%) postnatal ward with mother, nursery HDU, nursery
- Reason for admission: n(%) routine for mum and baby, maternal complication – baby admitted with mum, birth asphyxia, other
- Any antibiotics prescribed before enrolment since birth: n(%)
- Chlorhexidine cord care given: n(%)

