#### Primary analysis

- The primary analysis population is intention-to-treat, including all randomised participants, regardless of treatment received.
- The outcome variable will be change in Total log10 CFU from baseline to assessment time point.
- The primary analysis will include all randomised participants with baseline and at least one post-baseline measure.
- The dependent variable will be total log CFU.
- The model will be a mixed effects model
- Fixed effects in the model will be:
  - Antiseptic (1% CHG, 2% CHG, OCT)
  - Frequency of application (once, multiple)
  - Time point of assessment: hour of swab (continuous; mfp will be used to assess linearity)
  - Baseline total CFU (continuous; mfp will be used to assess linearity)
- Individual will be fitted as a random effect to account for repeated measures within individuals. Goodness of fit of an unstructured covariance matrix will be assessed and used if it is clearly a better fit to the data than random intercepts only.
- Goodness of fit of an interaction between baseline total CFU and timepoint of assessment will be assessed and included in the model if clearly a better fit.
- Normally distributed errors will be fitted.
- The intercept (reference treatment category) will be once only 1% CHG as this is the lowest concentration of CHG, which is believed to be more readily available than OCT, and so would be the most straightforward to implement. The standard of care control will not be used as the reference as the sample size for this arm is lower than for the factorial arms and so power for comparisons is correspondingly lower.
- Comparison of effects between factorial arms will be assessed by testing whether the null hypothesis of no treatment effect can be rejected (equivalent to using the estimate and 95% confidence interval of the estimate of the difference to the intercept).
- Comparisons between other arms and between arms and the SOC arm may also be performed. There will be no formal correction for multiple testing but interpretation will take multiple testing into consideration.
- Model fitting will use restricted maximum likelihood (REML) and p-values are derived using the Kenward-Roger approximation.

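### Admission ward, a recorded and plausibly prognostic factor, is left out of the randomisation and of the neonatal primary model; adding it would be a cheap precision gain of unknown size

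*Protocol*

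**What the plan says.** Protocol section 4.5.4 describes neonatal recruitment: "parents/carers will be approached after their baby has been admitted to the neonatal or post natal ward". The SAP's list of neonatal baseline variables (section 4.2) shows that the setting is recorded in three categories: "Where admitted: n(%) postnatal ward with mother, nursery HDU, nursery".

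The setting plays no part in allocation. Protocol section 4.5.5.1 states: "Randomisation will be by permuted blocks (random block sizes of 7 or 14 participants) to guard against bias introduced over time". No stratification factor is named there or in SAP section 2.5.

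It is also absent from the primary model. Protocol section 4.10.4 states: "Analysis will use linear mixed-models, with individual as a random effect, will adjust for baseline values of each outcome". SAP section 4.6 then fixes the covariates as antiseptic, frequency, hour of swab and baseline total CFU, with individual as a random effect.

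Ward does enter one later step. The subgroup part of SAP section 4.6 lists place of admission among nine neonatal subgroup factors. For each factor it adds a main effect to the primary model, and it fits the interactions with antiseptic and with frequency in separate models.

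Swabbing stops at discharge (Protocol section 4.7.1.2), and SAP section 1.2 warns that babies may "be discharged (in the neonatal strata) before all planned swabs are taken".

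**The concern.** The sponsor treats the hospital environment as a driver of the outcome. Blocking is justified by possible outbreaks over time, and Protocol section 4.6.2.1.2 points to environmental contamination in the postnatal period. Place of care is a natural companion to calendar time, yet only time is balanced.

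Baseline CFU removes ward differences present at time 0. Babies are enrolled under 24 hours of age, however, and the SAP appendix on informative priors reasons that load accumulates after birth. A ward difference could therefore develop after the baseline swab and remain in the residual.

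If it does, it adds to the error of the neonatal antiseptic and frequency contrasts, and a chance imbalance in ward mix would move an unadjusted estimate. Arms are small (21 each), and the factor is known before randomisation and already collected, so leaving it out of the primary model forgoes a possible gain for no evident saving.

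**Working it through.** **Step 1: the plan's own power figures.** Inputs are from Protocol section 4.5: 21 per arm, hence 42 per antiseptic, 63 per frequency and 21 controls, with differences in SD units.

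Power = Φ(d / √(1/n₁ + 1/n₂) − z₁₋α/₂)

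For two antiseptics, √(1/42 + 1/42) = 0.218, 0.82/0.218 = 3.758 and z for α = 0.012 is 2.512. Power = Φ(1.246) = 89.4%.

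| Contrast | n | α | Difference for 90% | Recomputed | Difference for 80% | Recomputed |
|---|---|---|---|---|---|---|
| Antiseptic v antiseptic | 42 v 42 | 0.012 | 0.82 | 89.4% | 0.72 | 78.4% |
| Frequency v frequency | 63 v 63 | 0.05 | 0.58 | 90.2% | 0.50 | 80.1% |
| Antiseptic v control | 42 v 21 | 0.012 | 1.01 | 89.7% | 0.88 | 78.3% |
| Frequency v control | 63 v 21 | 0.025 | 0.90 | 90.8% | 0.79 | 81.4% |

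All reproduce within two percentage points.

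**Step 2: what a ward term can remove.** Let p be the share of babies in one ward group and D the ward difference, in SDs, that remains after baseline adjustment. Neither is in the documents; both are assumptions. With total variance 1, ward accounts for p(1−p)D², so

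SE ratio (adjusted / unadjusted) = √(1 − p(1−p)D²)

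For p = 0.35, p(1−p) = 0.2275:

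| D (SD) | 1 − 0.2275·D² | SE ratio | SE reduction |
|---|---|---|---|
| 0.3 | 0.9795 | 0.990 | 1% |
| 0.5 | 0.9431 | 0.971 | 3% |
| 0.7 | 0.8885 | 0.943 | 6% |
| 1.0 | 0.7725 | 0.879 | 12% |

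**Step 3: repeated swabs.** The closed form treats each baby as one observation. Two mixed-model simulations let the number of swabs vary. Both assumed 126 babies in the six antiseptic arms, 35% in the nursery with three post-baseline swabs, postnatal babies with 0, 1 or 2 swabs in 20%, 50% and 30%, and within-baby correlation 0.5. SE ratios for ward effects of 0.3 / 0.5 / 0.7 / 1.0 SD were:

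- 400 replicates: antiseptic 0.98 / 0.96 / 0.93 / 0.87; frequency 0.99 / 0.97 / 0.94 / 0.89
- 2,000 replicates: antiseptic 0.99 / 0.98 / 0.93 / 0.88; frequency 0.99 / 0.97 / 0.94 / 0.88

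These agree with step 2 to within one or two points, provided the simulated ward effect is read as what remains after baseline adjustment. The swab counts by ward are assumptions too.

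**Step 4: in power and numbers.** Dividing the SD in step 1 by nothing but the step 2 ratio's effect (that is, using SD = √(1 − p(1−p)D²)), with p from 0.1 to 0.5:

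| D | Power, antiseptics at 0.82 SD | Power, antiseptic v control at 1.01 SD | Equivalent extra babies on 147 |
|---|---|---|---|
| 0 | 89.4% | 89.7% | 0 |
| 0.25 | 89.5-89.9% | 89.9-90.3% | 1-2 |
| 0.5 | 90.1-91.4% | 90.5-91.8% | 3-10 |
| 1.0 | 92.3-96.6% | 92.6-96.8% | 15-49 |

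The last column is 147 / (1 − p(1−p)D²) − 147. For example, p = 0.5 and D = 0.5 give 147/0.9375 − 147 ≈ 10.

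**Step 5: chance imbalance.** In 200,000 random allocations with no stratification by ward, the difference in ward share reached or exceeded in about 5% of trials was 12-21 percentage points for 42 v 42 and 17-26 points for 42 v 21 (p from 0.1 to 0.5). The shift in an unadjusted estimate is D times that difference: about 0.06-0.13 SD at D = 0.5 and 0.12-0.26 SD at D = 1.0, over both comparisons. The detectable differences are 0.82 and 1.01 SD.

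**The case against.** The strongest reply is that nothing here is wrong. A randomised comparison adjusted for the baseline outcome is valid, and simple blocking at one hospital is a defensible choice. Protocol section 4.10.4 leaves detail to the SAP, so on the protocol's own text only the unstratified allocation could be questioned. The SAP's subgroup step already fits the primary model plus a ward main effect, so a ward-adjusted estimate exists in the plan. SAP section 4 also flags baseline imbalances between randomised groups, so a marked ward imbalance would be seen. All of this stands, and it reduces the point to which of two planned estimates should be primary. An adjusted estimate found among nine subgroup analyses is not a substitute for adjusting the primary one.

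The assumptions also deserve challenge. The simulations give 70% of postnatal babies none or one post-baseline swab, yet SAP section 1.2 allows participants without a baseline and two post-baseline swabs to be replaced. A 1.0 SD residual ward effect would exceed the 0.82 SD antiseptic difference the trial is sized for. Both criticisms stand, so the upper end of the range is illustrative.

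Four stronger readings are tempting, and the documents do not support them:

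- **That the wards are known to differ in exposure or stay.** No section gives ward mix, contamination, length of stay or swab counts by ward. The difference is plausible, not documented.
- **That the contrasts are biased.** Randomisation prevents this. Chance imbalance is already covered, on average, by the unadjusted interval.
- **That power is overstated.** The planning differences are in SD units; if that SD is the total SD, ward variance is already inside it, and step 1 reproduces the figures.
- **That the missing-at-random assumption fails.** If discharge depends on ward but not on arm, and ward acts additively, the treatment contrasts remain unbiased. Nothing shows arm-dependent discharge, and Protocol section 4.7.6 says participation will not affect length of stay.

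**Conclusion.** The point holds as an optional improvement to the neonatal primary estimate, not as the correction of an error. Ward at enrolment is recorded, known before allocation and plausibly prognostic, but it is used only in a subgroup step.

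The gain is nil if no ward difference remains after baseline adjustment, and little below 0.3 SD. With 35% of babies in the nursery, the standard error falls by about 2-4% at 0.5 SD and about 12% at 1.0 SD. Ward share, residual ward effect and swab counts by ward are all assumptions, so the true gain cannot be fixed from these documents. The possible loss from adjusting is one degree of freedom.

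**What to change.** In SAP section 4.6, add place of admission at randomisation (postnatal ward v nursery/HDU combined, ignoring later transfers) as a fixed effect in the neonatal primary CFU model, and carry it into the Bayesian counterpart. The model already planned in the subgroup step then supplies the primary estimate; the interaction models can stay as they are. State the change before efficacy data are examined by arm.

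The cost is one line of text and one degree of freedom, with no new data. Keeping nursery and HDU as separate categories would cost two. The randomisation need not change. Extending the term to the skin-score and temperature models is optional; the calculations above do not address those outcomes.
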